## Stepwise Procedures

### Sample Size

To establish the sample size, we considered the effect sizes shown by the previous literature. Due to this study pretends to examine the efficacy of several types of interventions, we collected data from previous findings about brief therapies, transdiagnostic treatment, UP, conventional CBT, and combined therapy for the treatment of anxiety disorders and depression. A meta-analytic study examined the effect of various brief psychological therapies in comparison to usual GP care (Cape et al., 2010). The results of the meta-analysis to brief cognitive behavior therapy showed an effect size (Cohen’s *d*) of 1.06 for anxiety, 0.33 for depression and 0.26 for mixed anxiety and depression. In the case of brief counseling, the meta-analysis showed and effect size (Cohen’s *d*) of 0.41 to depression and 0.30 to mixed anxiety and depression. Another meta-analysis (Newby et al., 2015) studied the effect of transdiagnostic psychological treatment for depression and anxiety compared to waitlist, TAU and another psychological treatment, showing a large effect size (Hedges’ *g*) for both depression (*g* = 0.91) and anxiety (*g* = 0.85). Regarding UP, an RCT obtained an effect size (Hedges’ *g*) of 0.56 and 1.11 for anxiety and depression, respectively, using this treatment compared to waitlist (Farchione et al., 2012). Additionally, the findings of a recent meta-analysis about the effect of conventional CBT compared to waitlist, TAU or placebo showed an effect size (Hedges’ *g*) of 0.75 for depression, 0.80 for generalized anxiety disorder, 0.81 for panic disorder and 0.88 for social anxiety disorder (Cuijpers et al., 2016). By last, another meta-analysis examined the efficacy of combined therapies (psychotherapy plus pharmacotherapy) in comparison to pharmacotherapy for the treatment of anxiety disorders and depression (Cuijpers et al., 2014). The findings of this study showed an effect size (Hedges’ *g*) of 0.51 in favor of the combined therapy using CBT compared to pharmacotherapy only.

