Taking into account these results, a generalized medium effect size of 0.6 (Cohen’s *d*) was assumed to detect differences between the interventions and TAU. Due to software to calculate the sample size for analysis using mixed linear models is not available, we established the sample size for analysis of variance using the *f* index trough G^∗^Power. Therefore, we assumed an effect size of 0.3 (*f* index), equivalent to Cohen’s *d* = 0.6. Thus, with a statistical power of 0.80 and an alpha level of 0.05, a total sample of 140 participants will be required (28 subjects in each group). With the objective of controlling the lack of participants throughout intervention and evaluation process, based on previous studies (Farchione et al., 2012; Ito et al., 2016), we assumed an abandonment rate of 15%. Consequently, we require to include 165 participants in our study (33 participants per group).

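### The sample size equates f = 0.3 with d = 0.6, which cannot hold for five equal groups; a single intervention against TAU has about 60% power at d = 0.6, not 80%

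*Protocol article*

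**What the plan says.** The Sample Size section reviews published effects and settles on a medium effect of d = 0.6, which "was assumed to detect differences between the interventions and TAU". Because the authors had no software for mixed models, they write that "we established the sample size for analysis of variance using the" f index. The conversion is explicit: "Therefore, we assumed an effect size of 0.3 (*f* index), equivalent to Cohen’s *d* = 0.6". The result, "with a statistical power of 0.80 and an alpha level of 0.05", is that "a total sample of 140 participants will be required (28 subjects in each group"). A 15% abandonment rate then raises this to 165 (33 per group).

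Study Design confirms five groups, and the randomization paragraph gives equal allocation. The Present Study lists the hypotheses: ordered comparisons between named arms or sets of arms, several of them against pharmacological treatment, together with cost-effectiveness claims.

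**The concern.** The plan states its target as a standardised difference between the interventions and TAU, but the calculation is for an omnibus test across five groups. The two are linked only by the claim that f = 0.3 and d = 0.6 are the same effect. Halving d to obtain f is right for two equal groups, and for an even number of equal groups split half and half between two values. Five equal groups cannot be split that way.

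If the link fails, the 80% does not belong to the effect the plan names. A reader would take the chance of missing a true d = 0.6 between one intervention and TAU to be 20%, when on the plan's own simple basis it is about 40%. The Conclusion rests its case for implementing brief therapy partly on comparisons with pharmacological treatment, so the figure bears on how a null result would be read.

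**Working it through.** **Inputs.** From Sample Size: d = 0.6, f = 0.3, alpha 0.05, power 0.80, 140 evaluable (28 per group), 15% dropout. From Study Design and the randomization paragraph: k = 5 groups, equal allocation. The article does not say whether alpha is one- or two-sided; two-sided is used for contrasts between two arms, because the F test is non-directional.

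**1. The plan's own figure.** The one-way ANOVA F test has 4 and N − 5 degrees of freedom and noncentrality λ = N·f².
- N = 140, f = 0.30: λ = 140 × 0.09 = 12.6, power 0.809.
- N = 135: power 0.792. So 140 is the smallest balanced total reaching 0.80.
- Dropout: 140 / 0.85 = 164.7, rounded up to 165.

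Both stated totals reproduce, so what was computed is not in doubt.

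**2. The conversion.** For equal groups, f is the root mean square deviation of the group means from their overall mean, in units of the within-group SD.
- Two groups at 0 and 0.6: each lies 0.3 from the mean, so f = 0.3.
- TAU at 0 and four interventions at 0.6: mean 0.48; f = √[(0.48² + 4 × 0.12²)/5] = √(0.288/5) = 0.24.

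Other patterns, with omnibus power at N = 140:

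| Five group means (SD units) | f | Power |
|---|---|---|
| 0, 0.6, 0.6, 0.6, 0.6 | 0.240 | 0.59 |
| 0, 0, 0.6, 0.6, 0.6 (largest f for a span of 0.6) | 0.294 | 0.79 |
| 0, 0.15, 0.3, 0.45, 0.6 | 0.212 | 0.48 |
| 0, 0.3, 0.3, 0.3, 0.6 (smallest f for a span of 0.6) | 0.190 | 0.39 |
| 0, 0.4, 0.6, 0.6, 0.8 (average 0.6 against TAU) | 0.271 | 0.71 |
| 0, 0.3, 0.6, 0.6, 0.9 (average 0.6 against TAU) | 0.306 | 0.83 |

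The spacings in the last two rows are assumptions, chosen to follow the order in The Present Study. When the four interventions are equal, f = 0.4·d, so f = 0.30 corresponds to d = 0.30 / 0.4 = 0.75 against TAU.

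**3. One intervention against TAU.** Two-sample t test, 28 per group, noncentrality d·√(28/2).
- d = 0.6: 0.6 × 3.742 = 2.245; power 0.597 with 54 df, 0.606 with the pooled error df of 135.
- d = 0.51, the cited effect of combined therapy over pharmacotherapy alone: power 0.47.
- d = 0.33, the cited effect of brief CBT over usual GP care for depression: power 0.23.
- 80% power is reached at d = 0.76.

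**4. Sensitivity at d = 0.6.** One-sided 0.05 gives 0.72. Retaining all 33 per group gives 0.67. Neither reaches 0.80.

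**The case against.** Four arguments on the other side have force.

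*The omnibus power is not 0.59 as such.* That figure assumes four equally effective interventions, whereas the hypotheses rank them. If 0.6 is read as an average against TAU, omnibus power may be 0.71 or 0.83, depending on spacing. This stands: 0.59 is one pattern. It does not save the equivalence, since the article names no pattern and does not say that 0.6 is an average.

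*Not every hypothesis sets one arm against another.* Brief and conventional treatment are grouped against pharmacological treatment. If grouped arms share a mean 0.6 above TAU, 56 against 28 has 73% power, and all four interventions pooled, 112 against 28, has 80%. This also stands, so the 60% must be labelled as belonging to a single-arm contrast.

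*ANOVA is only a stand-in for the mixed model.* Adjustment for baseline could raise single-contrast power to about 64%, 72%, 79% or 87% at assumed baseline-outcome correlations of 0.3, 0.5, 0.6 or 0.7. The article states no correlation and takes no credit for one, so this does not validate its 80%. It does mean that 60% is not the proven power of the final analysis.

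*The choice of 0.6 is a judgement.* A reader might infer that 0.6 was obtained by averaging effects against waitlist. The article does not say that it averaged, and only the two figures from the Unified Protocol trial are against waitlist alone. The choice of effect size is separate from the conversion error.

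**Conclusion.** The stated equivalence is wrong for this design, and the 80% does not describe one intervention against TAU at d = 0.6. For that contrast, power is about 60% with 28 evaluable per group, two-sided 0.05, and no baseline adjustment. This is a shortfall of about 20 percentage points; 80% needs d of about 0.76. The step from f = 0.3 to 140 and the step to 165 are both correct.

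A reader might go further and infer that the trial is underpowered under its planned mixed model, that it must enrol more patients, or that contrasts with TAU should become the only basis of inference. The document supports none of these. Power under the mixed model depends on a correlation that is not given. The error can be corrected by stating the power truthfully at the planned size. The principal objective in Anticipated Results compares brief treatment with all four other arms, so restricting inference to TAU contrasts would leave part of it out. The article names no multiplicity correction, so none is applied here.

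**What to change.** In Sample Size:

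1. Delete the clause equating f = 0.3 with d = 0.6.
2. Say what the 80% refers to. Suggested wording: *With 140 evaluable participants, the five-group omnibus F test has 80% power at f = 0.30, which corresponds to d of about 0.75 against TAU if the four interventions are equally effective.*
3. Add the single-contrast power: *With 28 evaluable per group, a comparison of one intervention with TAU has about 60% power at d = 0.6 (two-sided 0.05, before baseline adjustment), 47% at d = 0.51 and 23% at d = 0.33; 80% power requires d of about 0.76.*
4. If a gain from the mixed model is to be claimed, state the assumed baseline-outcome correlation and the resulting power together.

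The cost is a few sentences and a less favourable stated power. The sample size, allocation and analysis are unchanged.

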### Target Population, Procedure, Randomization, and Blinding

We will include in our study patients with depression, anxiety or somatization disorder of mild to moderate severity. The detection of cases will be done from primary care by a GP. Patients that present these characteristics are encouraged to participate in the trial by de GP. Individuals who consent to participate and write the informed consent will receive the baseline assessment. If all eligibility criteria are fulfilled, the patient will be assigned randomly to one of the five groups according to a computer-generated allocation sequence (ratio: 1.1.1.1.1.). The randomization sequence will be generated prior to the recruitment of participants and will be conducted by a researcher uninvolved in the assessments of the study. At the end of treatment, there will be a post-treatment assessment and at 6-month follow-up. A single-blind process will be applied. The researcher in charge of the process of evaluation of the participants at the post-treatment and follow-up assessments are blinded to the intervention condition.

### Eligibility Criteria

#### Inclusion Criteria

In the study may be included any person between 18 and 65 years of age with a DSM-5 diagnosis of generalized anxiety disorder, agoraphobia, panic disorder, specific phobia, social anxiety (social phobia), anxiety disorder not otherwise specified, dysthymia, mayor depressive disorder, depressive disorder not otherwise specified and/or somatic symptom disorder. Besides, patient must meet predetermined cutoff points of mild to moderate severity level in at least one of the following assessment measures utilized: GAD-7 ≥ 10; PHQ-9 ≥ 10; PHQ-15 ≥ 5; PHQ-PD ≥ 8.

#### Exclusion Criteria

Patients with severe mental disorders (bipolar disorder and/or psychotic disorder), severe depression (PHQ ≥ 20), recent suicide attempts and/or current suicidal ideation, concurrent substance use disorder (alcohol, cannabis, stimulant, hallucinogen, and/or opioid), personality disorders, suspected or obvious mental retardation, and people who are taking pharmacological drugs that interferes with the Central Nervous System will be excluded.

### Ethics Statement

The study protocol (PSI2014-56368-R) has been authorized by the Ethics and Clinical Research Committee of the Ministry of Health of the Andalusia Government (Spain) and has been registered at clinicaltrial.gov with the number NCT03286881. This study is compliant with the General Data Protection Regulation (GDPR) of the European Union, potential study participants must provide written informed consent before they can be included in the study. The participants will receive written information regarding the study, including randomization to one of the study groups and the possibility of ending their participation at any time without disadvantages, before obtaining their informed consent. Participation in the study does not entail any danger for the participants except those related with pharmacological intervention. The engagement is voluntary and confidentiality is guaranteed.

### Interventions

#### Brief Psychological Treatment Based on UP

This intervention protocol consists of eight sessions according to an adaptation to brief format of the UP for the transdiagnostic treatment of EDs (Boisseau et al., 2010; Ellard et al., 2010; Barlow et al., 2011) and the NICE guideline “*Common mental health disorders”* (National Institute for Health, and Clinical Excellence [NICE], 2011). The treatment is developed by clinical psychologists in Specialized Care (SC). Each session has specific objectives:

S1.*Motivation for change and commitment to treatment*. The aim of the first session is to improve motivation for change analyzing the advantages and disadvantages of changing and defining determinants life goals.S2.*Understanding the function of emotions*. The second session gives information regarding the adaptive functions of emotions, introduces the concept of Emotion Driven Behaviors (EDBs) and distinguishes between thoughts, physical sensations and behaviors related to emotions.S3.*Emotional awareness training*. The third session aims to introduce and to practice emotional awareness centered on the present, without judging.S1.*Cognitive appraisal*. The objective of the fourth session is to teach appropriate thinking patterns, showing how to identify maladaptive ways of thinking and how to modify them.S4.*Emotional avoidance and EDBs*. The purposes of this session are to teach patients that emotional avoidance strategies favor the development and maintenance of EDs and help them to change their own maladaptive behaviors for others more appropriate and functional.S5.*Tolerance to physical sensations*. This session aims for the patient to get used to the physical sensations by performing exercises that causes these physical sensations, such as breathing through a straw.S6.*Interoceptive and situational emotional exposure*. The main of this session is to expose the patient to internal and external triggers that produce intense emotional reactions, in order to improve the habituation to emotions and decrease avoidance behavior.S7.*Conclusion and relapse prevention*. The objectives are to discuss the skills learned throughout the treatment, to identify the skills that should continue to be practiced in the future and to instruct how to face future situations.

#### Conventional Psychological Treatment

Patients in this group will receive the usual psychological treatment established within the healthcare process “Anxiety, Depression, and Somatizations” of the Andalusian Public Health Service (Spain) (Díaz del Peral et al., 2011). This treatment will be conducted in a range between 12 and 24 sessions of traditional CBT applied in a maximum period of 8 months. The treatment will be developed by clinical psychologists in Specialized Care (SC).

#### Conventional Psychological Treatment Plus Pharmacological Treatment

Patients in this group will receive the conventional psychological treatment based on traditional CBT, commented above, plus pharmacological treatment. The psychological treatment will be implemented by clinical psychologists and the pharmacological treatment will be prescribed by psychiatrist both in SC. This treatment will be carried out in a maximum period of 8 months.

#### Minimum Intervention Based on Basic Psychoeducational Information, Counseling, and Bibliotherapy

Patients in this experimental group will receive minimum psychological intervention based on basic psychoeducation, counseling and bibliotherapy by their GPs in PC. Previously, the GPs will have been trained by a clinical psychologist in how to give the patients basic information about their disorders, the use of strategies to face the basic symptoms of EDs without pharmacotherapy, and the use of bibliotherapy as support.

The minimum intervention will be conducted in a range between two to five sessions around 20–30 min long. Each session will be integrated by three components: (a) active listening and counseling; (b) psychoeducation about functioning and regulation of emotions; and (c) guided bibliotherapy. As a material for bibliotherapy, self-help guides of Andalusian Public Health Service^1^ (Spain) will be used considering the main symptoms of each patient.

#### TAU

The participants included in this experimental condition will receive the TAU prescribed by the GP in PC, based on pharmacotherapy exclusively. The GP will prescribe the TAU to the patient in a regular consultation. This consultation will usually consist of a session between 5 and 7 min in which the GP will evaluate the psychological and physical symptoms of the patients and will prescribe psychotropic drugs. This treatment will be carried out in a maximum period of 8 months.

## Proposed Analysis

The data will be analyzed following both intention-to-treat (ITT) and per protocol approaches. Firstly, ANOVA or chi-squared will be performed to compare the demographic variables and outcomes measures at baseline. Second, to examine longitudinal changes over time (baseline, posttreatment and follow-up) and between-group differences on these changes we will use linear mixed models, inasmuch as these models are more accurate than repeated-measures ANOVAs (Gueorguieva and Krystal, 2004). In the ITT analysis (all patients randomized are included in the analysis), the incomplete or missing data will be considered using the maximum likelihood estimation method. Additionally, Cohen’s *d* will be calculated to determine the size of between-group effects. Last, we will estimate the Incremental Cost-Effectiveness Ratio (ICER) to compare the relationship between costs and effectiveness of different interventions.

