## Materials and Equipment

### Study Design

This will be a multicenter randomized controlled trial (RCT) with five groups that will be realized in primary and specialized care centers from Córdoba (Spain) and its province. Patients will be randomly assigned to receive one of the following interventions: (a) *Brief psychological treatment based on UP*, (b) *Conventional psychological treatment*, (c) *Conventional psychological treatment plus pharmacological treatment*, (d) *Minimum intervention based on basic psychoeducational information, counseling and bibliotherapy*, and (e) *Active comparator treatment as usual (TAU): pharmacological treatment only*. For ethical reasons, in the case of low response to treatment, participants in the *Brief psychological treatment* and *Minimum intervention conditions* will be removed from the trial and will receive the treatment proposed by their GP. Outcome measures will be taken before randomization (baseline assessment), after the intervention (post-treatment assessment) and at 6-month follow-up. The overall study design is summarized in Figure 1. This RCT will be implemented following the SPIRIT guidelines (Chan et al., 2013a,b) and the CONSORT statement (Moher et al., 2010; Schulz et al., 2010).

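### As usually parameterised, the planned mixed-model contrast is a change-score comparison that does not use the pre-randomization baseline; it is unbiased but gives up precision that costs nothing to recover

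*Protocol article*

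**What the plan says.** Three statements in the protocol article bear on this point.

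- Study Design fixes the timing of the measurements: "Outcome measures will be taken before randomization (baseline assessment), after the intervention (post-treatment assessment) and at 6-month follow-up".
- Proposed Analysis begins with significance tests at baseline: "Firstly, ANOVA or chi-squared will be performed to compare the demographic variables and outcomes measures at baseline".
- The same section then gives the main model: "to examine longitudinal changes over time (baseline, posttreatment and follow-up) and between-group differences on these changes we will use linear mixed models". For the intention-to-treat analysis, "the incomplete or missing data will be considered using the maximum likelihood estimation method".

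The fixed effects are not listed. No baseline covariate is named and no constraint on the baseline means is mentioned. Nor does the text say that each arm has its own baseline mean, or that the baseline tests decide the model. No correlation between baseline and later scores is given.

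In Sample Size, "we established the sample size for analysis of variance using the" f index, with f = 0.3 treated as equivalent to d = 0.6. That calculation has no baseline term.

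**The concern.** The ordinary model for a between-group difference in change over three occasions has group, time and group-by-time effects. It estimates a separate baseline mean for each arm, and its contrast is then a comparison of change scores. Because baseline is measured before allocation, any difference between arms at baseline is due to chance. A model that uses this fact is at least as precise in large samples, and the natural reading of the plan does not use it.

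Precision matters here. The hypotheses are comparisons between particular arms, each arm is planned at 28 evaluable patients, and the Limitations section expects considerable dropout. When the baseline-outcome correlation is below 0.5, a change-score contrast is even less precise than a comparison of post-treatment scores that ignores baseline, which is in effect what the sample size calculation assumed.

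The baseline ANOVA and chi-squared tests are a smaller, related matter. With randomized allocation they test a null hypothesis known to be true, so their p-values answer no useful question.

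**Working it through.** **Inputs from the article:** five arms, 1:1:1:1:1; three occasions; f = 0.3 (taken as d = 0.6); alpha 0.05; power 0.80; 140 evaluable (28 per arm); 15% dropout; 165 enrolled (33 per arm).

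**Assumed, because the article gives no figure:** correlation ρ between baseline and outcome of 0.3 to 0.7; equal SDs at baseline and outcome, except in step 5.

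**1. The plan's own figure.** For a one-way ANOVA with 4 and N − 5 degrees of freedom and noncentrality f²N, N = 140 gives 0.09 × 140 = 12.6 and power 0.809. The smallest sufficient N is 138 (power 0.802), and the next multiple of 5 is 140. Then 140 / 0.85 = 164.7, so 165. Both stated figures reproduce.

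**2. Variance of a two-arm contrast, in units of 2σ²/n.**
- Difference in change, separate baseline means: 2(1 − ρ).
- Baseline as covariate, or common baseline mean: 1 − ρ².
- Ratio, adjusted to change: (1 + ρ)/2. Share of inverse variance lost: (1 − ρ)/2.
- Excess in standard error: √[2/(1 + ρ)] − 1.

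**3. Results.** Power is for d = 0.6 with 28 per arm, two-sided 0.05, by the normal approximation Φ(0.6 × √14 / √variance − 1.96).

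| ρ | Variance, change | Variance, adjusted | Inverse variance lost | SE excess | Power, change | Power, adjusted |
|---|---|---|---|---|---|---|
| 0.3 | 1.40 | 0.91 | 35% | 24% | 0.475 | 0.653 |
| 0.5 | 1.00 | 0.75 | 25% | 15.5% | 0.612 | 0.736 |
| 0.7 | 0.60 | 0.51 | 15% | 8.5% | 0.826 | 0.882 |

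A post-treatment-only comparison has variance 1 on this scale, so at ρ = 0.3 the change contrast has 1.4 times that variance.

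**4. Check in the full layout.** Generalised least squares for five arms and three visits, with separate against common baseline means, gives these losses at ρ = 0.3, 0.5 and 0.7:
- Complete data, same ρ at both later visits: 35%, 25%, 15%.
- 15% dropout, half of it before post-treatment: 33%, 24%, 14% at post-treatment and 32%, 22%, 13% at follow-up.
- Complete data, correlation decaying to ρ² by follow-up: 46%, 38%, 26% at follow-up.

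**5. Unequal SDs.** If the outcome SD is k times the baseline SD, the complete-data loss is (1 − ρk)² / (1 + k² − 2ρk).
- k = 1.25 (assumed): 22%, 11%, 2% at ρ = 0.3, 0.5, 0.7. For ρ = 0.3 this is 0.3906 / 1.8125.
- k = 0.8 (assumed): 50%, 43%, 37%. For ρ = 0.3 this is 0.5776 / 1.16.

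The size therefore depends strongly on quantities that the article does not give. The loss is never negative.

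**The case against.** The strongest reply is that the supposed fault is not in the text. The sentence lists three occasions and a difference in change but no parameterisation. A constrained longitudinal model also treats baseline as a response and also estimates differences in change, so the wording is compatible with the remedy proposed here. The article is condensed, and its full analysis plan may already constrain or adjust for baseline, in which case the loss is zero. This stands as a limit: separate baseline means are the natural reading, not a statement of the plan. It does not remove the point, because the article positively names the contrast and mentions no use of baseline to sharpen it.

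Other parts of the reply also stand, and they rule out stronger conclusions that a reader might draw:

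- **That the analysis is biased or invalid.** It is not. With baseline measured before randomization, the change contrast is unbiased.
- **That the plan loses a known 15% to 35%.** That range follows from assumed correlations and equal SDs. Equality is open to doubt, since the eligibility rules restrict baseline severity.
- **That true pairwise power is about 60%.** For the change contrast that holds only near ρ = 0.5. At ρ = 0.7 it is already above 0.80.
- **That the baseline tests cost precision or select the model.** The tests do not alter the contrast, and the article does not link them to model choice. Data-driven adjustment is a risk to avoid, not a stated plan.
- **That the sample size of 140 is wrong on this account.** It reproduces from its own inputs.

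**Conclusion.** The point holds as a matter of efficiency. If the mixed model gives each arm its own baseline mean, it forgoes precision that the design already supplies. With ρ between 0.3 and 0.7 and equal SDs, the loss is about 35% to 15% of inverse variance with complete data, and roughly 33% to 13% with 15% dropout and the same correlation at both later visits. At ρ = 0.5 the complete-data loss is equivalent to about a third more patients (1 / 0.75 = 1.33). The loss is larger if correlation decays by follow-up, and smaller or larger if the SDs differ. It is nil if the full plan already adjusts for baseline or constrains the baseline means.

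The baseline significance tests are stated outright and serve no purpose under randomization, but they are a minor issue. A change is worth making because the alternative is at least as precise in large samples and uses only data already being collected.

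**What to change.** State in the analysis section how baseline enters the model. Either of these serves:

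- the same linear mixed model over three occasions with one common baseline mean for all arms (constrained longitudinal model); or
- a mixed model with post-treatment and follow-up scores as outcomes and the baseline score as covariate.

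Present demographic variables and baseline scores descriptively by arm in place of the ANOVA and chi-squared tests, and say that baseline comparisons will not drive model choice. If the full plan already specifies one of the two models, a sentence saying so is enough.

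The cost is a sentence or two of wording. No extra patients, visits or data are needed.
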